#### Body composition

FM distribution, assessed by WHtR, and total FM are good predictors of cardiovascular disease [37], cardiometabolic disease [38] and some cancers including colorectal [39, 40], prostate [41], liver [42] and breast [43] cancers.

FFM has a high metabolic activity, plays a major role in metabolism (whole-body protein metabolism [44], post-prandial glucose uptake) and is the main determinant of resting energy expenditure [45].

Body composition will be evaluated in fasting conditions with a bioelectrical impedance (Tanita MC-780, USA, Arlington Heights) to determine absolute values of fat mass (FM) and fat-free mass (FFM). This device has shown a good reliability to obtain FM and FFM for adults [46] with different levels of PA [47] compared to measurements with dual-energy X-ray absorptiometry (DXA), considered to be the gold-standard method.

#### Physical fitness

Systematic review and meta-analysis reported that a low cardiorespiratory fitness is associated with higher risks of morbidity and mortality for people in good health [48, 49] or with chronic disease [50, 51]. Reduced muscle strength, as measured by grip strength, has also been associated with an increased risk of all-cause and cardiovascular mortality in socio-culturally and economically diverse countries [52].

Aerobic fitness will be evaluated with the Step Test. The step used for this test will be at a height of 16.25 inches (41.3 cm) for men and 11.8 inches (30 cm) for women. Stepping up and down will last for 6 min at the rate of 24 cycles per minute, set by a metronome. Subjects will wear a heart rate monitor Zephyr™ BioHarness™ (Zephyr Technology, Annapolis, USA) during the test. Heart rate will be recorded at the end of the test, after 30 s and 60 s of recovery. This test has been found reliable for healthy adults and is highly reproducible [53].

Low muscle mass and strength is associated with higher risk of mortality [54]. Muscle strength will be evaluated through upper and lower limb strength. A handgrip dynamometer will be used with dominant hand to assess upper limb strength. Three measurements will be made and only the best one will be registered. This method has already proved its efficiency and reliability with healthy adults [23, 55, 56] and in clinical use [57].

Lower limb strength will be assessed through a knee-extension power test on an isokinetic dynamometer (Biodex System 2, Biodex, Shirley, USA). Torque and power data will be corrected for gravity and will be digitized and exported at a rate of 2 kHz to an external data acquisition system (PowerLab 8/35; ADInstrument, New South Wales, Australia) driven by the LabChart 7.3 Pro software (ADInstrument, New South Wales, Australia). This isokinetic dynamometer has been validated and found reliable for isometric and concentric assessment [58, 59]. Subjects will be seated comfortably with a hip joint at 105° of flexion and will be attached on the trunk, the hip and the left leg to the dynamometer chair with Velcro straps to provide a complete stability during every maximal contraction. The dynamometer lever arm will be attached to the right leg by a strap positioned 1–2 cm above the lateral malleolus. Torque will be measured at a knee joint angle of 90°. Participants will perform three isometric 3 s-Maximum Voluntary Contraction (MVC) with 2 min of rest between each try. Peak torque values will be checked during data collection and an additional test will be done when there is a torque variation higher than 10% between the three tests. Then, only the best one will be reported.

Concentric torque will also be measured during three MVCs performed at a velocity of 60°/s and 120°/s. The extension will be at their maximal abilities when the flexion will be done at their own comfort speed. Between the two different velocities, subject will have 2 min of rest. Only the best peak power will be reported.

#### Metabolic outcomes

Large volumes of SB sedentary time increase cardiometabolic risks and inflammatory biomarkers [60]. Reducing SB with an increasing of PA are more favourable to preserve metabolic health [61, 62].

Basal blood samples will be drawn after a 12-h overnight fast by a nurse. It will be asked to every subject to keep their usual daily activities. However, they will be instructed to avoid high intensity exercise and stressful situations on the day before the test and to avoid caffeine consumption and nicotine in the morning before the test.

Blood will be centrifuged and plasma will be kept frozen in aliquots at − 80 °C until analysis in batch. All samples will be shipped to laboratories on dry ice at each end of evaluation period (T0, T1, T2).

Lipids profile and inflammatory markers will be measured using a Dimension Vista® system (Siemens Healthcare GmbH, Erlangen, Germany). Plasma triglycerides will be measured with Dimenson Flex™ reagent cartridges (inter-assay CV = 3% at 68 mg/dL, 2% at 384 mg/dL) (intra-assay CV = 4% at 68 mg/dL, 2% at 384 mg/dL). Plasma LDL-cholesterol will be assessed with Dimenson Flex™ reagent cartridges (inter-assay CV = 2% at 50 mg/dL, 2% at 145 mg/dL) (intra-assay CV = 4% at 50 mg/dL, 4% at 145 mg/dL). Plasma HDL-cholesterol will be measured with Dimenson Flex™ reagent cartridges (inter-assay CV = 1.6% at 47 mg/dL, 1.9% at 69 mg/dL) (intra-assay CV = 2.3% at 47 mg/dL, 2.1% at 67 mg/dL). Plasma glucose will be measured with Dimenson Flex™ reagent cartridges (inter-assay CV = 2% at 75 mg/dL, 1% at 379 mg/dL) (intra-assay CV = 3% at 75 mg/dL, 2% at 379 mg/dL). Plasma insulin will be assessed with IMMULITE® 2000 System (inter-assay CV = 7.3% at 7.67 μIU/mL, 5% at 26.4 μIU/mL) (intra-assay CV = 5.5% at 7.67 μIU/mL, 3.9% at 26.4 μIU/mL). Insulin resistance will be determined with the use of the homeostasis model assessment of insulin resistance (HOMA-IR) [63]. Plasma high sensitivity C-reactive protein will be measured with Dimenson Flex™ reagent cartridges (inter-assay CV = 4.8% at 0.115 mg/dL, 5.4% at 0.346 mg/dL) (intra-assay CV = 4% at 0.115 mg/dL, 4.4% at 0.346 mg/dL).

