## Hypothesis

We hypothesize that the daily use of a cycling workstation for 3 months will increase PA and reduce SB on both working and non-working days and will improve physical and psychological health outcomes compared to a control condition with no intervention. The addition of three extra months of intervention (i.e. 6 months total) will further improve the study parameters compared to the effects that will be observed after 3 months of intervention.

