**Fig. 1 Fig1:**
[figure not shown]
Study overview

Eighty tertiary employees from Clermont-Ferrand (France) will be recruited to participate in this protocol. Three worksites of moderate size (*n* = 80 employees across the 3 sites) will be randomly assigned to one of the two interventions: (1) CTL_PPM3, an intervention with two consecutive periods: 3 months with no change of working conditions (CTL: control phase) and 3 months of PPM use (PPM3), and (2) PPM6, an intervention with 6 months of PPM use. Tests will be performed on both groups at baseline (T0), after 3 (T1) and 6 months (T2) of the intervention. Information sheets will be given to all the participants and written informed consent will be obtained for each participant. This study has been approved by the ethical authorities (CPP IDF VIII 19 09 66) and registered as a clinical trial under the reference number NCT04153214 (clinicaltrials.gov).

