The comparisons between the randomized groups will be performed (1) as aforementioned for continuous secondary endpoints and (2) using the chi-squared or Fisher exact tests for categorical variables. For non-Gaussian data, results will be presented using median difference and 95% confidence intervals estimated using quantile regression model. For categorical parameters, the results will be expressed using absolute differences and 95% confidence intervals. The multivariable analysis associated to dichotomous endpoints will be generalized linear mixed model, with logit link function, and centre as random-effect. As secondary endpoints will be exploratory, no type I error correction will be applied, but the results will be expressed with odds ratios and 95% confidence intervals.

Longitudinal data will be analysed using random-effects regressions, modelling between and within patient effect, as random-effect, in addition to centre effect. The following fixed effects will be studied: randomization group, time-points evaluation and their interaction.

According to clinical relevance and to the European Medicines and Consolidated Standards of Reporting Trials recommendations, planned subgroup analyses will be proposed after completion of the study. *Subgroup × randomization group* interaction will be added to the in regression models with factors such as gender or age used for the subgroup analysis.

Particular attention, mainly descriptive, will be paid to study the adherence of participants and identify barriers and challenges to their motivations and ability to perform the PA intervention. A sensitivity analysis will be performed to study the statistical nature of missing data and to determine the most appropriate approach to the imputation of missing data: maximum bias (e.g. last observation carried forward, baseline observation carried forward) or estimation proposed by Verbeke and Molenberghs for repeated data. A study of patients’ abandoning will be proposed considering this parameter as a censored data, and consequently using the Kaplan-Meier to estimate it and log-rank for the comparison between groups.

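### Wave-by-wave shipment of blood samples may tie assay run to visit; if so, within-arm change over time in insulin/HOMA-IR, CRP and anandamide is open to run-to-run shift

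*Protocol article*

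**What the plan says.** On handling, the Metabolic outcomes section says that "plasma will be kept frozen in aliquots at − 80 °C until analysis in batch" and then: "All samples will be shipped to laboratories on dry ice at each end of evaluation period (T0, T1, T2"). It does not say when the laboratories run the assays, how many runs there are, or how samples are allocated to runs.

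On timing, the Study design section says: "Tests will be performed on both groups at baseline (T0), after 3 (T1) and 6 months (T2) of the intervention". PPM6 cycles throughout. CTL_PPM3 starts cycling at T1.

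On the questions asked, the Hypothesis section has two parts. The first is a 3-month effect "compared to a control condition with no intervention". The second is that three further months "will further improve the study parameters compared to the effects that will be observed after 3 months of intervention". The Objectives section extends the 6-month question to all listed outcomes, including the blood markers.

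On analysis, the Statistical analyses section plans between-group comparisons and a random-effects model for the longitudinal data: "The following fixed effects will be studied: randomization group, time-points evaluation and their interaction". It calls the secondary endpoints exploratory.

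On assay precision, the article gives for insulin "inter-assay CV = 7.3% at 7.67 μIU/mL, 5% at 26.4 μIU/mL" and for CRP "inter-assay CV = 4.8% at 0.115 mg/dL, 5.4% at 0.346 mg/dL". For anandamide it gives only upper limits, below 12% between assays and below 10% within.

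**The concern.** Frozen storage, batch analysis and a shipment after each wave together suggest one batch per visit. Under that arrangement batch and visit are the same variable, so no batch term can be estimated and no later analysis can separate a calibration shift from a true time effect.

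Two results would be exposed: the time effect in the longitudinal model, and the 3-to-6-month gain if it is read as the change from T1 to T2 within PPM6. The T1-to-T2 change in CTL_PPM3, which is that arm's own 3-month response, is exposed in the same way. Every sample in a wave shares the shift, so more participants do not dilute it. They shrink the standard error and make a false rejection more likely.

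**Working it through.** **The plan's own figure.** The article gives no figure for this comparison. Its only sample-size statement (18 per group, effect size 1, two-sided 5%, power above 80%) concerns PA and SB. It reproduces, with *t*-test power 0.83 at 18 per group, and is not in dispute.

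**Inputs from the article (inter-assay / intra-assay CV).**
- Insulin: 7.3% / 5.5% at 7.67 μIU/mL; 5% / 3.9% at 26.4 μIU/mL.
- CRP: 4.8% / 4% at 0.115 mg/dL.
- Anandamide: below 12% / below 10%.
- Triglycerides: 3% / 4% and 2% / 2%. LDL: 2% / 4% at both levels. HDL: 1.6% / 2.3% and 1.9% / 2.1%. Glucose: 2% / 3% and 1% / 2%.

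**Inputs assumed.**
- One run per visit.
- SD of within-person change, s, of 30-40% of the mean.
- n per arm of 20 (the per-arm figure in the sample-size section) to 36. The 36 is 80 participants in two arms, 40 each, less the loss implied by the article's step from 18 to 20: 40 × 18/20 = 36.
- The inter-assay CV stands in for the shift between waves.

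**Formulas.**
- Between-run CV: at most the inter-assay CV. If that figure includes within-run error, it may be as low as √(inter² − intra²).
- SD of the shift between two visits: d = √2 × between-run CV.
- Standard error of the mean change: SE = s/√n.
- False-rejection rate of a nominal 5% T1-to-T2 test: 2(1 − Φ(1.96 × SE/√(SE² + d²))).

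**Standard errors.** For n = 36: 30/6 = 5.0% and 40/6 = 6.7%. For n = 20: 30/4.47 = 6.7% and 40/4.47 = 8.9%.

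**Results.**

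| Marker and CV used | Between-run CV | d | n = 20 | n = 36 |
|---|---|---|---|---|
| Insulin, 7.67 μIU/mL, inter-assay | 7.3% | 10.3% | 20-29% | 29-39% |
| Insulin, 7.67 μIU/mL, √(7.3² − 5.5²) | 4.8% | 6.8% | 12-17% | 17-25% |
| Insulin, 26.4 μIU/mL, √(5² − 3.9²) | 3.1% | 4.4% | 8-10% | 10-14% |
| CRP, 0.115 mg/dL, inter-assay | 4.8% | 6.8% | 12-17% | 17-25% |
| CRP, 0.115 mg/dL, √(4.8² − 4²) | 2.7% | 3.8% | 7-9% | 9-12% |

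Within each cell the lower rate belongs to s = 40% and the higher to s = 30%.

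**Anandamide.** At the 12% limit, d = 17.0% and the rate could reach 58% (n = 36, s = 30%). Subtracting one upper limit from another bounds nothing, so there is no lower figure.

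**Lipids and glucose.** At every listed level the intra-assay CV equals or exceeds the inter-assay CV, so the subtraction leaves no positive between-run component. Even with the full inter-assay CV, d is only 2.3% for HDL (CV 1.6%), 2.8% for LDL and glucose (CV 2%) and 4.2% for triglycerides (CV 3%).

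**Which contrasts are affected.** A simulation of 10,000 trials with one shared shift per visit (insulin CV 7.3%, s = 20%, 40 per arm) gave these rejection rates under no true effect: within-arm T2 against T1, 56.5%; between arms at T2, 5.2%; group × time, 5.1%. A shift common to both arms cancels from the last two.

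**The case against.** The strongest reply is that the article fixes when samples are shipped, not when or in how many runs they are assayed. The laboratories could hold all three waves and run them together. Run allocation and bridging controls are details that a condensed article commonly leaves to a laboratory manual, so their absence is no fault in itself. This stands, and it makes the point conditional.

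A reader might infer that the 3- against 6-month biomarker comparison as a whole is invalid. The article does not support that. The Hypothesis section does not say that the comparison is made within an arm. At T2, PPM6 has had 6 months of use and CTL_PPM3 has had 3, measured at the same visit, so the design holds a randomised 6-versus-3-month contrast from which a common shift cancels. Between-group comparisons are already planned. The group × time interaction is also safe, although it does not itself estimate the 3-to-6-month gain, because CTL_PPM3 begins cycling at T1.

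Three further limits stand:
- No arm is untreated between T1 and T2, so a within-arm change has other time-related explanations that same-run assay would not remove.
- The markers are secondary and exploratory.
- The size depends on assumptions. With k independent runs per visit and samples split evenly, d falls to √(2/k) × CV; two runs would take insulin from 10.3% to 7.3%.

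What the reply does not remove is that the stated shipping rule points towards assay by wave, that time is listed as a fixed effect to be studied, and that the article does not say which contrast will carry the 3-to-6-month conclusion.

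**Conclusion.** The point holds conditionally and is minor. If each wave is assayed on arrival, within-arm change over time cannot be separated from run-to-run shift for insulin/HOMA-IR, CRP and anandamide. On the stated assumptions, false rejection of a nominal 5% T1-to-T2 test is about 12-39% for insulin from the CV at 7.67 μIU/mL. It is about 10-14% from the lower-bound CV at 26.4 μIU/mL with 36 per arm, and about 7-25% for CRP. The anandamide figure is unbounded below. Lipids and glucose give little or no demonstrable problem.

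The concurrent comparison at 3 months, the comparison of PPM6 with CTL_PPM3 at T2, the interaction and the accelerometer outcomes are untouched, provided both arms share the runs of each wave. The SD of within-person change, the single run per visit and the 36 per arm are not stated in the article, so the ranges show scale rather than a prediction.

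**What to change.** Replace the three shipments with one. Keep all aliquots at -80 °C, already the stated storage, until T2 is complete. Then assay each participant's T0, T1 and T2 samples in the same run, with both arms in every run. The shift then cancels from within-person change, the T1-to-T2 test returns to its nominal 5%, and the sample size does not change. If the laboratories already plan joint assay, one sentence saying so closes the point.

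The Trial status section reports recruitment finished in March 2021, so earlier waves may already have been assayed. In that case, either re-run retained T0 or T1 aliquots beside the T2 samples as bridging samples, if any remain, or state that the 6-versus-3-month biomarker conclusion rests on the between-arm contrast at T2 and report within-arm changes as descriptive.

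The cost is one sentence, about six months' longer storage of the T0 samples, and later laboratory results. The bridging option adds repeat assays. The T2-contrast option costs nothing in the laboratory but gives up inference on within-arm change.

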#### Stress and anxiety

High levels of SB have been associated with increased risks for mental disturbances [64] such as stress [65], depression [66, 67] or anxiety [68]. On the other hand, meta-analysis demonstrated that regular PA decreases anxiety [69] and depression [70]. Stress and anxiety will be measured by questionnaires and objective methods (blood anandamide levels and heart rate variability). Plasma N-arachidonylethanolamine, also known as anandamide (AEA), is a lipid which is involved in pain perception, anxiety and depression and in stress response [71]. It has been shown that anxiety inversely correlates with blood AEA levels in humans [72, 73]. Blood AEA will be measured by enzyme-linked immunosorbent assay (ELISA) (Clound-Clone Corporation, Houston, TX, USA) (inter-assay CV < 12%, intra-assay: CV < 10%; detection range 2.47–200 ng/mL).

Heart rate variability is a cardiovascular risk marker [74] associated with burnout [75] and chronic stress [76]. It is also an indirect measure of autonomic nervous system [77, 78]. It will be evaluated during 24 h with heart rate monitor Zephyr™ BioHarness™ (Zephyr Technology, Annapolis, USA), and analysed according to the “Task Force recommendations” [79].

Stress level at work [80] and at home will be assessed by a visual analogic scale (VAS) on a horizontal line of 100 mm, ranging from very low (1—no stress) to very high (100—maximal stress).

Equanimity is the ability to have an attentional, emotional and cognitive balance of the mind [81]. This parameter will be evaluated with the Two Factor Equanimity Scale (EQUA-S), which has been validated [82].

#### Quality of life at work and job strain

A socio-ecological approach suggests to evaluate individual behaviour with a multiple level factors focused on the social and physical environment [83]. Reducing SB with an increasing of moderate-to-vigorous PA can be a strategy to improve the quality of life (QOL) [84]. To our knowledge, no study has assessed the effect of increasing light PA and reducing SB on the worksite on QOL.

The Job Content Questionnaire is one of the most widely used questionnaires; it relates the characteristics of a workplace to health and well-being [85] and relies on the demand-control model [86]. This test has shown a good reliability with middle-aged adults [87]. The imbalance between high efforts spent at work and low rewards received will be assessed by the effort-reward imbalance (ERI) questionnaire designed by Siegrist [88]. This questionnaire has also been validated in this population [89].

Pain will be evaluated by the Nordic Musculoskeletal Questionnaire (NMQ) [90, 91]. This questionnaire has been validated in working population [92] including office workers [93].

To evaluate the QOL at work, five different VAS for mental and physical fatigue, burnout, life and sleep quality will be used. These VAS will be on a horizontal line of 100 mm, ranging from very low (1) to very high (100) [77].

### Exploratory outcomes

#### Resting metabolic rate and cycling energy expenditure

Resting metabolic rate (RMR) will be measured by indirect calorimetry (FitMate™ -COSMED, Rome, Italy) [94]. This method with FitMate™ device has been validated in healthy adults [95]. Before the test, gas analysis will be calibrated following the instructions of the manufacturer’s recommendations. Subjects will stay 20 min in a chair and remain calm in a quiet place. O2 consumption will be measured for 15 min minimum and the last 5 min will be reported [96]. RMR will be calculated using the Weir’s equation [97].

Participants will undergo a 30-min exercise testing using the DeskCycle device. The objective will be to demonstrate that this exercise is of light-intensity. It will also allow to observe whether there is a metabolic adaptation after 3 and 6 months of using the PPM. During the exercise testing, energy expenditure and substrate utilization will be calculated by measuring gas exchange by indirect calorimetry with a portable device (MetaMax 3b; Cortex Biophysik, Leipzig, Germany). This device has been validated for gas exchange measurements during exercise [98]. Before each test, gas analysis will be calibrated according to the manufacturer’s recommendations. Subject will be seated in a comfortable position to pedal and in a thermoneutral environment. The resistance will be set at 2 and RPM at 50 during the whole test. Gas exchange will be measured for 30 min. Energy expenditure will be derived from calorimetry-measured VO2 and VCO2 using Weir’s equation [97]. Substrate utilization will be derived using Peronnet and Massicotte equation [99].

#### Eating behaviours

Modern sedentary behaviours are known to promote food overconsumption [100, 101], which coupled with low levels of energy expenditure can favour chronic positive energy balance and long-term weight gain. The effect of the intervention on eating behaviours will be determined using two complementary questionnaires [102]. A revised version of the Three-Factor Eating Questionnaire (TFEQ R21) [103] will be used to assess three different domains: uncontrolled eating, emotional eating and cognitive restraint. Answers will be coded following the instruction of Cappelleri et al. [104]. The Dutch Eating Behaviour Questionnaire (DEBQ) will also be used for assessing three different domains: external, restrained and emotional eating. Answers will be coded following the instruction of Lluch et al [105]. Both questionnaire exist in French language and have been adapted to the French population [103, 105, 106].

